### Research aim

The primary aim is to estimate the proportion of women infected with chlamydia who fail treatment with 1 gram azithromycin, the most widely recommended first line treatment for genital chlamydia infection [18-20]. The secondary aim is to determine the role of *C. trachomatis* organism load, azithromycin tissue absorption of azithromycin and antimicrobial resistance in chlamydia treatment failure.

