### Participant eligibility

Women who are diagnosed with genital chlamydia and who meet eligibility criteria will be invited to participate in the study. The study is limited to women because of their increased risk of serious chlamydia related complications.

The inclusion criteria are:

• Female;

• Positive test for genital chlamydia using Nucleic Acid Amplification Test polymerase chain reaction [PCR] (performed on specimens collected from women recruited from Sydney Sexual Health Centre) or strand-displacement assay (performed on specimens collection from women recruited from Melbourne Sexual Health Centre);

• Age ≥16 years;

• Adequate English and comprehension skills to give informed consent;

• Able to attend their recruitment clinic for follow up and specimen collection at day 7;

• Resides in a jurisdiction serviced by one of the two clinics and plan to stay in the jurisdiction for the next 8 weeks.

The exclusion criteria are:

• Current infection detected as a part of a routine test for re-infection [18];

• Concomitant infection with another bacterial STI;

• Concurrent PID;

• Self report of antibiotic use in the last 2 weeks;

• Current commercial sex work;

• Women who do not wish to receive study packs by post;

• Women who do not have a mobile phone;

• HIV positive status;

• Concurrent medication likely to significantly interact with azithromycin (e.g. cyclosporine, digoxin);

• Known macrolide allergy.

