### Recruitment

Women who have tested positive for chlamydia will be seen by a research nurse at a participating clinic at point of treatment. The research nurse will explain the study to them, assess eligibility and take informed consent. The research nurse will collect specimens for further testing (Table 1) and provide treatment with a single dose of 1 gram azithromycin. The nurse will observe the participant as she takes her treatment to ensure compliance. This is classified as the baseline visit (Day 0). All clinic visits, pathology costs and treatment for participants and their partners will be provided free of charge.

**Table 1 T1:** Specimen collection by study timeline.

**Specimen collection and testing**										**If PCR positive @ d28, 42 or 56**
Day	0^d^	7	14	21	28	35	42	49	56	
Number of swabs collected	4	2	2	2	2	2	2	2	2	4-5
Culture	X									X
PCR^a^	X	X	X	X		X		X		X
Chlamydia organism load^a^	X	X	X	X	X	X	X	X	X	X
Genotype^a^	X	X	X	X	X	X	X	X	X	X
Sequencing^a^	X	X	X	X	X	X	X	X	X	X
Y-chromosome^a^		X	X	X	X	X	X	X	X	X
β-globin^a^	X	X	X	X	X	X	X	X	X	X
Test of cure^b^					X		X		X	
Az absorption^a^		X								
Blood	X									X
Rectal swab^c^										X
Location	Clinic^e^	Clinic^e^	Home^f^	Home^f^	Home^f^	Home^f^	Home^f^	Home^f^	Home^f^	Clinic^e^

^a^Processed in batches throughout the course of the study.

^b^Chlamydia PCR done in real time to report results back to participants and treat any women diagnosed chlamydia positive.

^c^If anal sex reported.

^d^Day 0 = baseline or at time of recruitment.

^e^Swabs collected by research nurse and put immediately into the appropriate medium.

^f^Self-collected high-vaginal swabs.

Key: X = specimen processed for this experiment, PCR polymerase chain reaction, Az *absorption* azithromycin absorption, d day.

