### Primary outcome

The primary outcome is the proportion of women who are classified as having chlamydia treatment failure following detection of chlamydia on a self-collected high-vaginal specimen using a polymerase chain reaction (PCR – see below) Specimens will be collected for testing on days 28, 42 or 56 after recruitment (referred to as ‘test of cure’ specimens for the purpose of this study) according to the algorithm in Figure 1. This algorithm follows a previously described method [10] with the addition of the detection of Y chromosome DNA and performing high discriminatory chlamydial genotyping. Y chromosome DNA will be used to validate sexual behaviour data because it can be detected in the vagina for up to 14 days after unprotected intercourse with a male partner [25,26]. Specimens will be collected from participants every 7 days for Y chromosome detection and genotyping will be undertaken on any chlamydia positive specimens collected on days 28, 42 or 56 after recruitment. Chlamydial genotype fingerprinting will be performed to determine any differences in chlamydia strain/serovar between a participant’s baseline specimen and any repeat positive specimens detected at day 28, 42 or 56 [27]. If a woman has the same serovar present at follow up, further testing by multilocus sequence typing (MLST) targeting *ompA* and five house-keeping genes will be undertaken [28,29]. Detection of same MLST type without detection of Y chromosome DNA or any reports of unprotected sex will be classified as treatment failure. If the woman has a different serovar, it will be classified as a re-infection. A repeat positive chlamydia diagnosis will also be classified as a re-infection if the woman’s repeat specimen has the same MLST type and Y chromosome is detected or she reports unprotected sexual contact.

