### Genotyping & quantification of organism load

Chlamydial fingerprinting will be conducted on specimens that are PCR positive at baseline and at test of cure. We will determine the organism load, identify the chlamydia serovar(s) (genovar) of each infection through a series of quantitative PCR assays to establish whether or not the genotype of the chlamydia detected in those women who have a repeat positive is the same as the type present at baseline [27]. Initial qPCR primers and probes have been designed to predict antigenic differences in major outer membrane protein (MOMP) to determine the serovar as previously described [27,36-38]. The primary chlamydia group-specific multiplex quantitative PCR will target conserved regions of the *ompA* gene specific to all chlamydia serovar groups, including the B group (serovars B, E, D, L1, and L2), C group (serovars A, C, H, I, J, K, and L3) or intermediate group (serovars F and G) serovars. This assay will enable quantification of organism load and will be used to direct serovar-specific PCRs to determine serovars present in the specimen, including possibility of mixed serovars [27,39].

Chlamydia organism load in each specimen will be quantified by comparing the crossing-threshold of each specimen to the crossing-threshold of a standard curve constructed by amplifying different known copy numbers of the *ompA* gene. The beta globin gene, present at one haploid copy per nucleated cells [40], will also be quantified using qPCR to assess specimen adequacy as well as to measure sampling variability between participants and specimens by correlation with the number of eukaryotic cells collected. The quantity of chlamydia will be divided by the number of eukaryotic cells and expressed as the number of organisms present per 100 eukaryotic cells [40].

Specimens from participants where the same serovar has been detected at baseline and follow up will undergo further discriminatory confirmation of relatedness using sequencing of *ompA* gene, as well as five house-keeping genes (*hctB,* CT058, CT144, CT172, and CT682 [*pbpB*]) utilizing a multilocus sequence typing (MLST) approach [28,29,41,42]. This will include the amplification and sequencing [29,43,44] followed by determining MLST type using *C. trachomatis* MLST database (mlstdb.bmc.uu.se).

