### Statistical analysis

The population risk of treatment failure will be estimated as the observed proportion of women in the sample with treatment failure, with 95% CI calculated assuming an underlying binomial distribution. Multinomial logistic regression will be used to explore the association between the three-level outcome variable (treatment failure, treatment success, re-infection) and risk factors such as the impact of organism load, azithromycin absorption and MIC. One advantage of a multinominal model over two separate logistic regression models (one comparing the prevalence of treatment failure with treatment success, the other comparing the prevalence of re-infection with treatment success) is that the question of whether treatment failure and re-infection share common risk factors can be addressed formally by comparing estimated odds ratios generated by the same model. Linear regression analyses will investigate trends in chlamydia organism load over time and explore any associations with symptoms, chlamydia serovar and participant age. Both linear and multinomial regression models will be implemented with fixed and random regression effects to accommodate the longitudinal and repeated measures nature of the data. All analyses will be conducted in Stata 12.0.

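### Women PCR-negative at day 0 cannot meet the written failure rule but are not removed from the primary denominator, so the failure proportion is biased down by an unknown amount

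*Protocol article*

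**What the plan says.** The Research aim section sets the target: "The primary aim is to estimate the proportion of women infected with chlamydia who fail treatment with 1 gram azithromycin".

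The inclusion criteria in Participant eligibility ask for a positive diagnostic nucleic acid test: PCR for women recruited in Sydney, a strand-displacement assay for those recruited in Melbourne. Recruitment comes after that result: "Women who have tested positive for chlamydia will be seen by a research nurse at a participating clinic at point of treatment". New swabs are taken at that visit, which the same section makes the study baseline. Table 1 lists PCR, organism load and genotype on the day-0 swabs, with the footnote "Processed in batches throughout the course of the study". No exclusion criterion concerns a negative day-0 swab.

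Under Primary outcome, strains are compared between the participant's "baseline specimen and any repeat positive specimens detected at day 28, 42 or 56". A match on multilocus sequence type, with no Y-chromosome DNA and no reported unprotected sex, is a failure. A different serovar is a re-infection, and so is a matching type with evidence of exposure. The Genotyping section adds: "Chlamydial fingerprinting will be conducted on specimens that are PCR positive at baseline and at test of cure". The Study endpoint section allows three outcomes only: failure, re-infection or success.

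The estimator in Statistical analysis is "The population risk of treatment failure will be estimated as the observed proportion of women in the sample with treatment failure", with a binomial 95% confidence interval.

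**The concern.** The numerator and the denominator are drawn from different groups. Only women with a typable day-0 specimen can be counted as failures, but the denominator has no such condition. A woman who tested positive at diagnosis and is PCR-negative when treated adds to the denominator and can add nothing to the numerator.

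The study is meant to show whether failure is nearer 8% than the 2–3% of older culture-based work (Discussion). A denominator that includes women who cannot fail pulls the estimate towards the lower benchmark. Recruiting more women does not reduce this shift, and the binomial interval does not reflect it.

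**Working it through.** **The plan's own figure.** Sample size estimates gives 450 women for a risk of 8% with limits of 5.5% and 10.5%. With n = z²p(1 − p)/d², z = 1.96, p = 0.08 and d = 0.025, n = 3.8416 × 0.0736 / 0.000625 = 452.4, or 453. At n = 450 the normal-approximation interval is 5.49% to 10.51%. The stated figure reproduces to within rounding and is not in dispute.

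**Following a day-0-negative woman through the written rules.**
1. She has a positive diagnostic test, so she is eligible.
2. Her day-0 PCR is run in a later batch, so she is enrolled and treated before the result is known.
3. If her tests of cure are negative, the only one of the three endpoints that fits is success.
4. If a test of cure is positive, neither a matching sequence type nor a different serovar can be shown, because there is no baseline type. The text gives her no class.
5. In both cases she is not a failure, and no sentence removes her from the sample.

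**Direction.** Let f be the share PCR-negative at day 0 and p the failure risk in women PCR-positive at day 0. The written estimator expects p(1 − f). Suppose a share g of all women (g ≤ f) are infected but missed by the day-0 swab, with failure risk q. The risk in all infected women is then [p(1 − f) + gq] / [(1 − f) + g]. Its numerator is at least p(1 − f) and its denominator is at most 1, so it is never below p(1 − f). This source of error therefore cannot push the estimate up, whether or not the day-0 negatives were truly uninfected.

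**Size.** The article gives neither f nor the interval from test to treatment. The values of f below are assumptions. The last two columns restrict the 450 to day-0 positives, with half-width 1.96 × √(0.08 × 0.92 / n).

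| f (assumed) | Expected if p = 8% | Expected if p = 3% | Women left of 450 | Half-width at 8%, points |
|---|---|---|---|---|
| 5% | 7.6% | 2.85% | 428 | 2.57 |
| 10% | 7.2% | 2.7% | 405 | 2.64 |
| 15% | 6.8% | 2.55% | 383 | 2.72 |
| 20% | 6.4% | 2.4% | 360 | 2.80 |

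At f = 10% the shift is 0.8 points, about a third of the planned half-width (0.8 / 2.5 = 0.32). The expected estimate would fall below the planned lower limit of 5.5% only if f exceeded 1 − 5.5/8 = 31%.

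**The case against.** Several counter-arguments carry weight.

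- **The plan does not say these women are kept.** A reader might infer that the article states that day-0 negatives stay in the denominator and are counted as cures. It does not. It distinguishes 450 required from 520 recruited, so the sample is not simply everyone recruited. Figures 1 and 2, to which classification is referred, are not shown here and could contain a restriction, as could a separate analysis plan. This limits the point to the written text. It does not remove it, because the estimator, the failure rule and the three endpoints are all stated, and applied together they do not give the quantity in the aim.
- **The genotyping sentence is weak evidence of intent.** It may only describe which paired specimens are compared. It does not show that the authors expected day-0 negatives. The point needs only that the failure rule requires a baseline type.
- **Failure per diagnosed and treated woman is a coherent quantity.** The cohort is described as women who test positive, and the Discussion applies the failure rate to national case counts. That is a good reason to report the unrestricted proportion too. But the stated aim concerns infected women, and even the unrestricted quantity is missed if some day-0 negatives are infected, since their failures cannot be counted.
- **A negative day-0 swab need not mean no infection.** Swabs outside the test-of-cure days are frozen in buffer and extracted later, and the Melbourne eligibility assay is a different one. A low-load infection could be missed. This stands, and it is a real drawback of the fix.
- **The share is assumed.** This also stands. Even at 20% the expected 6.4% lies inside the planned interval, and no planned conclusion is shown to change.

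**Conclusion.** The concern holds for the written text. Women PCR-negative at day 0 can enter the denominator but not the numerator, so the estimated failure proportion is biased down relative to the stated aim. A day-0-negative woman with a positive test of cure has no written class.

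The direction follows from the rules. The size does not: on an assumed day-0-negative share of 5% to 20%, a true 8% is expected as 7.6% to 6.4%. The documents do not support saying that the bias is large or that day-0 negatives were uninfected. The verdict assumes that the figures not shown, and any separate analysis plan, add no restriction. It is worth correcting because the correction is cheap and uses assays already planned.

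**What to change.** In Statistical analysis, define the primary denominator as women whose day-0 specimen is chlamydia PCR-positive and who have a test-of-cure result. Report the number PCR-negative at day 0. Use beta-globin there only to separate negatives on an adequate specimen from inadequate specimens. It should not be an entry condition for PCR-positive women, since that would discard valid participants. Give the all-recruited denominator as a sensitivity analysis, and say how a day-0-negative woman with a positive test of cure is counted in it. Fix this wording before the batched day-0 results are analysed.

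The change needs no new visit, specimen or assay. Its costs are:
- Fewer evaluable women and a slightly wider interval: about 405 women and a half-width of 2.64 points, against 2.5 planned, if 10% are negative.
- Possible selection: if some day-0 negatives are low-load false negatives, the restricted set leans towards higher-load women. If load raises the risk of failure, the restricted estimate could then lie somewhat above the risk in all infected women. The article should state this, and reporting both denominators lets the reader judge it.

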### Data analysis

#### Sample size estimates

To detect a treatment failure risk of 8% with a 95% CI of 5.5%, 10.5%, 450 women are required. If the risk of treatment failure is observed to be 3% (as reported by the earlier meta-analysis [22]), then a sample size of 450 generates a 95% CI of (1.7%, 5.0%). To account for a loss to follow up of 15% based on previous studies [8], 520 women will be recruited.

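### Same-strain failures in exposed women are coded as re-infection, so the planned odds-ratio comparison leans towards finding shared risk factors

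*Protocol article*

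**What the plan says.** The Primary outcome section classifies repeat positives by strain and by evidence of exposure:

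- Failure: "Detection of same MLST type without detection of Y chromosome DNA or any reports of unprotected sex will be classified as treatment failure".
- Re-infection by strain: "If the woman has a different serovar, it will be classified as a re-infection".
- Re-infection by exposure: it also counts as re-infection where her "repeat specimen has the same MLST type and Y chromosome is detected or she reports unprotected sexual contact".

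The Study endpoint and Statistical analysis sections keep three outcomes, with no indeterminate class. The multinomial model relates them to "risk factors such as the impact of organism load, azithromycin absorption and MIC". The same factors appear in the secondary aim, which ends with the role of "antimicrobial resistance in chlamydia treatment failure". As one advantage of the model, the plan says that "whether treatment failure and re-infection share common risk factors can be addressed formally by comparing estimated odds ratios generated by the same model".

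**The concern.** The re-infection class holds two kinds of women. Some carry a different strain, which is direct evidence of a new infection. Others carry the baseline strain and have some sign of exposure; these may be re-infected by the same partner or may be failures who also had sex. The rule cannot separate the two and sends all of them to re-infection. Abstinence is advised for only 7 days of a follow-up of up to 56 days (Partner notification), so exposure among true failures is plausible.

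Organism load, absorption and MIC are the candidate causes of failure. If one of them does raise failure, the misplaced failures carry that association into the re-infection class. A formal comparison of the two odds ratios may then suggest a shared risk factor where there is none.

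A second, conditional problem has the same source. Failure can occur only in unexposed women, whereas success includes exposed and unexposed women. A covariate associated with exposure is therefore associated with the failure label even if it has no effect on failure.

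**Working it through.** **The plan's own figures.** "To detect a treatment failure risk of 8% with a 95% CI of 5.5%, 10.5%, 450 women are required". The Wald formula gives n = 1.96² × 0.08 × 0.92 / 0.025² = 452.4, or 453, against 450. The sample size is not in dispute. The plan gives no figure for the odds-ratio comparison, so what follows rests on stated assumptions. From the plan come the 8% and 3% failure risks, N = 450 and the classification rule.

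**Assumptions, not in the documents.** A binary factor with 50% prevalence; failure odds ratio 3; true re-infection odds ratio 1; exposure independent of the factor. The base case has 40% of women unexposed and 6% true re-infection.

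**Base case at 8% failure.** True class probabilities that meet these conditions:

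| | Failure | Re-infection | Success |
|---|---|---|---|
| Factor absent | 4.25% | 6.24% | 89.51% |
| Factor present | 11.75% | 5.76% | 82.49% |

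The rule moves the exposed 60% of failures into re-infection:

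- Factor absent: 6.24 + 0.6 × 4.25 = 8.79%.
- Factor present: 5.76 + 0.6 × 11.75 = 12.81%.
- Observed re-infection odds ratio: (12.81/82.49) / (8.79/89.51) = 1.58, where the truth is 1.
- Observed failure odds ratio: (4.70/82.49) / (1.70/89.51) = 3.0, unchanged.
- Share of the re-infection class that is misplaced failure: 0.6 × 8 / (0.6 × 8 + 6) = 44%.

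In general, the observed re-infection odds ratio is (1 − w) × true re-infection odds ratio + w × failure odds ratio, where w is the misplaced share of the re-infection class among women without the factor. Here w = 2.55/8.79 = 0.29, and 0.71 × 1 + 0.29 × 3 = 1.58. The pull is always towards the failure odds ratio; only its size depends on the assumptions.

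**Range.** The same calculation over 30–70% unexposed and 3–10% re-infection:

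| True failure | 10% re-infection, 70% unexposed | Base case | 3% re-infection, 30% unexposed |
|---|---|---|---|
| 8% | 1.22 | 1.58 | 1.98 |
| 3% | 1.09 | 1.26 | 1.52 |

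**Effect on the test.** This uses 20,000 simulated studies of 450 women and two-sided 5% Wald tests. Re-infection is set here as a risk among cured exposed women. With 8% failure, failure odds ratio 3, 50% exposed and a 10% re-infection risk, about 18 women are classed as failure and 39 as re-infection, 18 of whom are true failures.

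- A false association of the factor with re-infection is declared in 28% of studies, against about 4% with correct classes.
- Power to show that the two odds ratios differ is 12%, against 46%. Part of this loss comes from the smaller failure class.
- Over six scenarios (3% or 8% failure, failure odds ratio 2 or 3, re-infection risk 5–20%, 50% or 70% exposed), false association occurs in 8–36%. Power is 3–21%, against 22–62% with correct classes.

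**Covariates associated with exposure.** Suppose that 30% of women with a covariate and 60% without it are unexposed, and that the covariate has no effect on failure. With no re-infection, the failure-versus-success odds ratio is 0.30/0.60 = 0.50. With re-infection risk up to 20% among cured exposed women it is 0.50–0.53. If the unexposed share is the same in both groups, it cancels and no such bias arises, as the unchanged 3.0 above shows.

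**The case against.** Several points on the other side stand.

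- The analysis is exploratory and secondary. The plan calls the comparison one advantage of the model, not its sole purpose, and the binomial estimate of the failure proportion does not use the model.
- The exposed share, the re-infection risk and the failure odds ratio are all assumed. At the plan's own 3% scenario the distortion can be small (1.09).
- A reader might infer that the failure odds ratios for organism load, absorption and MIC carry a spurious exposure effect. The documents do not support this: nothing in them links these factors to sexual activity. Sexual-practice data are collected and the list of risk factors is open, so an exposure-related covariate could be modelled, but the text does not say that one will be.
- Different-strain re-infection is not a neutral comparator. The abstract names an untreated partner as a source of repeat infection, and that partner would usually pass on the same strain.
- Small counts limit the comparison in any case. In the base case about 14 of 450 women are classed as failure (450 × 0.032) and 27 are true re-infections. If half of those are different-strain (an assumption), the contrast with failure has an expected z of about 1.4, against about 1.0 for the planned one.

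Two objections do not stand. That an analysis plan would supply the detail does not help, because the rule and the inference drawn from it are both stated and they conflict. That the rule is cautious about calling failure may be so for the failure proportion, but in this comparison it creates association. The algorithm figure is not shown, but the text states the rule in words.

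**Conclusion.** The point holds in a limited form. The stated classification biases the failure-versus-re-infection comparison towards shared risk factors for any factor that raises failure but not re-infection. The direction follows from the rule alone. The size rests on assumed inputs: with a failure odds ratio of 3 and a true re-infection odds ratio of 1, the observed re-infection odds ratio is about 1.2–2.0 at 8% true failure and about 1.1–1.5 at 3%. Failure-versus-success odds ratios are biased only for covariates associated with sexual exposure. A reader might go further and conclude that most of the re-infection class is misplaced failure. The documents do not show that: in the base cases the share is 44% at 8% failure and 23% at 3% (1.8/7.8), and the true share depends on figures the plan does not give.

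**What to change.** In the multinomial analysis, use four levels: success; same-strain unexposed (failure); same-strain exposed (indeterminate); and different-strain re-infection, by serovar or MLST type. Report the shared-risk-factor comparison of failure with different-strain re-infection alongside the planned three-level result. Add bounds that count the indeterminate class as all failure and as all re-infection; the second bound is the planned analysis.

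For covariates associated with exposure, estimate failure versus success within unexposed women only. Adjusting for exposure in the full model will not work: by definition no exposed woman can be a failure, so exposure perfectly predicts non-failure and its coefficient cannot be estimated.

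The genotype, Y-chromosome and behaviour data are already being collected, so this needs only recoding. The price is smaller cells and wider intervals. Because the different-strain class omits re-infection by the same untreated partner, that comparison should be read as a sensitivity analysis and not as a replacement.

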### Study endpoint

A study participant will reach the study endpoint when she is diagnosed with treatment failure, re-infection or treatment success. The study endpoint will be measured by a test of cure PCR conducted after 28, 42 or 56 days follow up according to Figure 2.

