### Azithromycin absorption

High-vaginal specimens collected by the research nurse at the day 7 visit will be preserved in 1 ml of 100% methanol and stored at −80°C prior to analysis. Azithromycin levels are thought to remain well above the reported MIC for chlamydia for between 10 to 14 days post-treatment with 1 g dose [30,31]. Azithromycin levels in high-vaginal material (cells and mucus) will be measured using a validated liquid chromatography – tandem mass spectrometry method (LC-MS/MS) [47-50]. An azithromycin standard curve will be prepared in high-vaginal specimens from a separate individual not exposed to azithromycin, and azithromycin concentrations detected by LC-MS/MS will be normalised to lipid concentrations [50]. Azithromycin concentrations in high-vaginal specimens will be normalised to membrane lipid concentrations and then calculated using the standard curve.

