### Data collection

Participants will be asked to complete questionnaires at the time of recruitment and each week until they reach study endpoint. The following data will be collected:

• Age, height, weight

• Genital symptoms

• Reason for attending clinic for their initial test

• Current medications including contraceptives and concurrent antibiotics

• Date of last menses

• Sexual practice data including number of sexual partners, type of sexual partners (casual, occasional, once off or regular), type of sexual contact (vaginal or anal sex), condom use; and

• Whether partners have been notified and treated

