### Loss to follow up

The provision of reimbursement payments throughout the study is paramount to maximize retention. Women will be reimbursed with vouchers totalling up to $100 to cover their transport and time costs during the study. This will be broken down into smaller payments, $25 at their first follow up visit, $10 for their day 14 specimen, $10 for their day 21 specimen, $25 for their day 28 specimen and then $30 upon completion of the study (day 56 specimen or earlier if repeat positive). Reimbursements will reflect how many specimens and questionnaires are returned.

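### Random effects are prescribed for the multinomial endpoint model as if its outcome were repeated, but each woman has one terminal classification, so a woman-level variance is at best weakly identified

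*Protocol article*

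**What the plan says.** The Statistical analysis section of the protocol article plans two kinds of regression. A multinomial logit relates "the three-level outcome variable (treatment failure, treatment success, re-infection" to "risk factors such as the impact of organism load, azithromycin absorption and MIC". A linear regression follows organism load over time. One sentence then covers the two together: "Both linear and multinomial regression models will be implemented with fixed and random regression effects", and the purpose is "to accommodate the longitudinal and repeated measures nature of the data". No other level of clustering is named.

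Elsewhere the article fixes how often the endpoint is observed:

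- Study endpoint: "A study participant will reach the study endpoint when she is diagnosed with treatment failure, re-infection or treatment success".
- Data collection: questionnaires are completed "each week until they reach study endpoint".
- Loss to follow up: the last payment is made "upon completion of the study (day 56 specimen or earlier if repeat positive".

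Azithromycin absorption is also measured once, from "High-vaginal specimens collected by the research nurse at the day 7 visit".

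**The concern.** A random effect for the woman separates variation between women from variation within them, and so needs more than one outcome per woman. Weekly organism load supplies that. The endpoint classification does not: it is a single label that closes her follow-up. Repeated covariates do not make the outcome repeated.

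Without replication, a larger assumed variance can be offset by larger coefficients with almost no change in fit. The odds ratios for load, absorption and MIC would then depend on where the optimiser stops and not on the data. The section also plans a formal comparison of the odds ratios for failure and for re-infection, and that comparison can be affected as well.

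**Working it through.** **Size of the data set.** The plan's evaluable number reproduces. With p = 0.08 and half-width 0.025, n = 1.96² × 0.08 × 0.92 / 0.025² = 452.4, against 450 stated. With 450 women the interval is 5.49% to 10.51%. The sample size is not in dispute and is used here only as N. Expected failures are 0.08 × 450 = 36.

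**Outcomes per woman.** The Study endpoint section makes the classification terminal. Questionnaires stop there, and completion is day 56 or an earlier repeat positive. A woman therefore contributes one classification.

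**Method.** A three-category logit was fitted by maximum likelihood to simulated data on 450 women with one outcome each. A normal random intercept per woman was integrated by 31-point quadrature, with its SD fixed in turn. Assumptions not taken from the documents: re-infection about 6%, true odds ratio 2.0 for failure and 1.5 for re-infection.

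**Binary covariate, shared intercept**

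| SD | log-likelihood | OR failure | OR re-infection |
|---|---|---|---|
| 0 | -227.9237 | 2.20 | 1.82 |
| 0.5 | -227.9237 | 2.25 | 1.86 |
| 1 | -227.9237 | 2.41 | 1.99 |
| 2 | -227.9237 | 3.06 | 2.52 |
| 3 | -227.9237 | 4.17 | 3.44 |

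The likelihood is exactly flat. Two covariate groups with two free probabilities each are already fitted perfectly by four fixed parameters, so nothing is left to estimate a variance. With independent intercepts per category the likelihood is again -227.9237 throughout, while the failure odds ratio runs from 2.20 to 3.95 and the re-infection odds ratio from 1.82 to 2.60.

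**Continuous covariate, shared intercept.** From SD 0 to SD 3 the log-likelihood moves from -244.6978 to -244.9192, so twice the difference is 2 × 0.2214 = 0.44. Over the same range the failure odds ratio goes from 1.91 to 3.26 and the re-infection odds ratio from 1.56 to 2.70. In 60 simulated studies, twice the log-likelihood difference between SD 2 and SD 0 had a median absolute value of 0.20, a 95th percentile of 0.85 and a maximum of 1.30, all well below 3.84. The failure log odds ratio grew by a median factor of 1.39.

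**Scaled to a marginal odds ratio of 2.0 (assumed).** From the binary table:

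- SD 1: ln 2.41 / ln 2.20 = 1.116, and 2^1.116 = 2.17.
- SD 2: ln 3.06 / ln 2.20 = 1.418, and 2^1.418 = 2.67.

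The continuous-covariate median factor at SD 2 gives 2^1.39 = 2.62.

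**Comparison of failure with re-infection.** In the binary case the ratio of the two odds ratios is 2.20/1.82 = 1.21 at SD 0. At SD 3 it is 4.17/3.44 = 1.21 with a shared intercept and 3.95/2.60 = 1.52 with independent intercepts.

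**When the SD is estimated.** In 100 further simulated studies with a continuous covariate and a shared intercept, 52% of fits fell to an SD near 0, which is the ordinary logit. In about a quarter the SD exceeded 4 and the failure log odds ratio was at least 2.4 times its ordinary-logit size. With a binary covariate, the fit stayed near its starting SD of 0.5, with log odds ratios about 3% larger. The exact shares depend on seed and optimiser; the pattern does not.

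**The case against.** The strongest reply is that this is one condensed sentence in an article, and that the level of the random effects and the data layout are commonly left to an analysis plan that is not shown. That would answer a complaint about missing detail. Here, however, the article states a choice for both models and gives a reason that does not apply to one of them. A clinic effect does not rescue the sentence either: the stated reason is repeated measurement, and there are only two clinics.

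The second reply is that the rows could be test-of-cure occasions on days 28, 42 and 56, with weekly covariates that vary over time. Figure 2 is not shown, so this layout cannot be excluded. A reader might infer that it would be wrong because failure and re-infection end follow-up. That does not follow. Event-free rows up to a terminal event are how a discrete-time competing-risks model is built. A woman-level term there is a frailty, which is debatable but not wrong on that ground, and this layout was not simulated. It would still be an event model with at most one event per woman, not repeated classifications.

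Three other strong readings fail:

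- **The variance can never be estimated.** This is exact only for categorical, saturated covariates. The named risk factors are quantitative, and there the variance is weakly identified.
- **The model is bound to fail or to inflate.** About half of the continuous-covariate fits simply returned the ordinary logit.
- **A general approximation gives the size.** Multiplying the log odds ratio by √(1 + 0.346 SD²) turns 2.0 into 2.23 at SD 1 and 2.92 at SD 2. The fitted three-category model gives the smaller 2.17 and 2.67.

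**Conclusion.** Wrong as written. The stated reason for random effects does not hold for the multinomial endpoint model. With one terminal classification per woman, the variance is unidentified for categorical covariates and weakly identified for continuous ones. The result may be the ordinary logit or may be inflated odds ratios. For an assumed marginal odds ratio of 2.0 and a shared intercept, the range is about 2.2 at SD 1 to about 2.7 at SD 2, with the data barely distinguishing the two. These sizes rest on the assumed odds ratios, the assumed re-infection rate, N = 450 and a normal random intercept for the woman.

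The damage is limited to the exploratory risk-factor odds ratios and to the comparison of failure with re-infection, the latter at least if the intercepts are not shared. A reader might infer that the main result or the whole secondary aim is at risk. The documents do not support that. The primary outcome is a binomial proportion, the sample size rests on its interval, and the section on further classification of treatment failure assigns causes without any regression. Random effects remain appropriate for organism load over time.

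**What to change.** Restrict the random-effects sentence to the longitudinal organism-load (linear) model. For the endpoint, specify an ordinary multinomial logit with one row per woman, clinic as a fixed effect, and each repeated covariate reduced to a pre-specified value such as baseline load. If visit timing or time-varying covariates are wanted, specify instead a discrete-time competing-risks multinomial model over days 28, 42 and 56 with visit-specific intercepts.

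This changes a sentence or two of the analysis text. It needs no extra data, specimens or participants.
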